## Abstract

**Background:**

Patients with major depression disorder presents increased rates of cognitive decline, reduced hippocampal volume, poor sleep quality, hypertension, obesity, suicidal ideation and behavior, and decreased functionality. Although continuous aerobic exercise (CAE) improves some of the aforementioned symptoms, comorbidities, and conditions, recent studies have suggested that performing aerobic exercise with motor complexity (AEMC) may be more beneficial for cognitive decline, hippocampal volume, and functionality. Therefore, this randomized controlled trial will compare the effects of CAE and AEMC on depression score, cognitive function, hippocampal volume, brain-derived neurotrophic factor expression, sleep parameters, cardiovascular risk parameters, suicidal behavior, functionality, and treatment costs in patients with depression.

**Methods/design:**

Seventy-five medicated patients with depression will be recruited from a Basic Healthcare Unit to participate in this prospective, parallel group, single blinded, superiority, randomized controlled trial. Patients with depression according to DSM-V criteria will be balanced and randomly assigned (based on depression scores and number of depressive episodes) to a non-exercising control (C), CAE, and AEMC groups. The CAE and AEMC groups will exercise for 60 min, twice a week for 24 weeks (on non-consecutive days). Exercise intensity will be maintained between 12 and 14 points of the rating of perceived exertion scale (~ 70–80% of the maximum heart rate). The CAE group will perform a continuous aerobic exercise while the AEMC group will perform exercises with progressively increased motor complexity. Blinded raters will assess patients before and after the intervention period. The primary outcome measure will be the change in depression score measured by the Montgomery-Asberg Depression Rating Scale. Secondary outcomes will include measures of cognitive function, hippocampal volume, brain-derived neurotrophic factor expression, sleep parameters, cardiovascular risk parameters, suicidal behavior, functionality, and treatment costs.

**Discussion:**

This study was selected in the call of public policy programs for the Brazilian Unified National Health System – “PPSUS 2015”. To our knowledge, this is the first pragmatic trial to test the effect of adding AEMC to the pharmacological treatment of patients with depression and to evaluate the possible reductions in depression symptoms and healthcare costs.

**Trial registration:**

Brazilian Clinical Trials Registry (ReBec) - RBR-9zgxzd - Registered on 4 Jan. 2017.

**Electronic supplementary material:**

The online version of this article (10.1186/s13063-018-2906-y) contains supplementary material, which is available to authorized users.

## Background

Major depressive disorder (MDD) is a mood disorder characterized by several behavioral and emotional symptoms, such as depressed mood, irritability, anhedonia, psychomotor agitation or lethargy, insomnia or hypersomnia, decreased appetite, fatigue, and suicidal ideation and behavior [1]. This disorder is a global health burden in which the cost of the traditional pharmacological treatment will reach approximately US$ 91 billion in 2030 [2]. In addition to direct costs, MDD usually occurs in association with several comorbidities.

Epidemiological and review studies have reported a relation between depression and decreases in cognitive function [3–6], brain volume, and expression of brain-derived neurotrophic factor (BDNF) [7]. In addition, the odds ratio of sleep disturbances (1.42 to 3.23), short sleep duration (1.41 to 2.53) [8], metabolic syndrome (1.58), and obesity (1.27) [9, 10] is significantly higher for MDD patients than for the general population. Furthermore, 9 out of 10 suicides are related to psychiatric illness [11, 12], with depression being observed in two-thirds of them [13].

As a large portion of patients with depression do not properly respond to drug treatment (30% response without remission, 20% partial remission and 50% remission) [14], alternative interventions should be added to standard drug treatment aiming to improve the health status of patients. Non-pharmacological synergic interventions, such as physical exercise, have been deemed effective to mitigate the burden of depression and associated comorbidities [15, 16]. Accordingly, physical exercise has been widely recommended as an effective non-pharmacological intervention for depression, cognitive function, hypertension, obesity, and type 2 diabetes [17, 18]. The effectiveness of physical exercise to decrease the burden associated with these conditions has been confirmed by several systematic reviews and meta-analyses [16, 19–22]. For example, Cooney et al. [16] (35 studies, 1.353 subjects) and Wegner et al. [19] (32 studies, 48,207 subjects) reported that aerobic exercise can reduce depression symptoms (effect sizes of 0.62 and 0.56, respectively). Smith et al. [20] (31 studies, 2.049 patients with depression) demonstrated that physical exercise produces small improvements (in elderly people) in indices of cognitive function, such as attention and processing speed (effect size 0.16), executive function (effect size 0.12), and memory (effect size 0.12). Furthermore, Cornelissen and Smart [21] found a reduction in systolic blood pressure of healthy adults after aerobic exercise (93 studies, 5223 subjects).

Even though continuous aerobic exercise (CAE) seems to produce beneficial effects on depression and associated comorbidities, recent studies have shown that physical exercise with high motor complexity may produce additional benefits to overall health status. Specifically, exercise with high motor complexity may be particularly beneficial for patients with depression as it requires high levels of attention, memory, and motor difficulty, producing greater cortical activation than exercises with low motor complexity (e.g., CAE) [23, 24]. Accordingly, high cortical activity (i.e., due to the integration of perceptual, motor, and cognitive information) has the potential to produce greater neuroplasticity [25] (i.e., changes in brain structure and function) than conditions requiring low cortical activity (low motor complexity). Recent studies from our group demonstrated that 3 months of an exercise program with high motor complexity produced greater cognitive improvement in patients with Parkinson’s disease than exercises with low motor complexity [26]. In addition, hippocampal volume seems to increase after an exercise intervention with high motor complexity (i.e., coordinative exercises) [27]. This finding is particularly important as increases in hippocampal volume are associated with improved brain function, while decreases in hippocampal volume are related to depression symptoms [27].

Taken together, it is reasonable to suggest that high motor complexity aerobic exercises may produce greater health benefits (depression score, cognitive function, hippocampal volume, BDNF expression, sleep parameters, cardiovascular risk parameters, suicidal behavior, functionality and treatment costs) than low motor complexity aerobic exercises (e.g., cycling, running). Thus, we hypothesized that aerobic exercise with motor complexity (AEMC) will be more effective than CAE in improving outcomes of cognitive decline, hippocampal volume, BDNF expression, sleep parameters, cardiovascular risk parameters, suicidal behavior, functionality, and treatment costs in patients with depression undergoing standard drug treatment.

## Methods/design

### Study design

This prospective, parallel group, single-blinded, superiority, randomized controlled trial will compare the effect of 24 weeks of either CAE or AEMC added to standard pharmacological treatment of patients with major depression in the Brazilian primary care system (Additional file 1 - SPIRIT 2013 Checklist) Fig. 1. Changes in depression score, cognitive function, hippocampal volume, BDNF expression, sleep parameters, cardiovascular risk parameters, suicidal behavior, functionality, and treatment costs will be assessed. It will be a single-blinded study since the researchers performing the assessments and statistical analyses will be blinded to treatment allocation. The expected start and completion dates are April 2018 and December 2018, respectively.

**Fig. 1 Fig1:**
[figure not shown]
Template of recommended content for the schedule of enrolment, interventions, and assessments

The primary outcome will be the change in the Montgomery-Åsberg Depression Scale (MADRS) score [28]. Secondary outcomes will be (1) cognitive function, assessed by Frontal Assessment Battery score [29], Trail Making Test A and B score [30], Rey’s Auditory-Verbal Learning Test (RAVLT) score [31], Digit Symbol Substitution Test score [32], Montreal Cognitive Assessment (MoCA) score [33], and Stroop test score [34]); (2) hippocampal volume assessed by magnetic resonance imaging (MRI) [35]; (3) BDNF expression [36]; (4) sleep parameters assessed by Pittsburgh Sleep Quality Index score [37], sleep quality assessment by accelerometry and the Biological Rhythms Interview of Assessment in Neuropsychiatry (BRIAN) score [38]; (5) cardiovascular risk assessed by global cardiovascular score, metabolic syndrome, waist circumference, blood pressure, lipid profile (total cholesterol, HDL cholesterol, LDL cholesterol, triglycerides), and glycemia [39, 40]; (6) suicidal ideation and behavior assessed by the Scale Columbia of Suicide score [41] and Scale of Hopelessness score [42]); (7) functionality assessed by gait linear spatial variables [43, 44], Timed Up and Go test (TUG) score [45], TUG cognitive score [46], handgrip strength [47], 6-min walk test [48] physical activity levels (sedentary time, active time, time spent in different physical activity intensities, energy expenditure, and number of steps per day), body weight, and hip and waist circumference [49]; and (8) treatment costs including laboratory procedures, medicines, and doctor consultations per patient [50].

The study will be conducted in accordance with theDeclaration of Helsinki revised in 2008 [51] and approved by the ethics committees of the Department of Health of the city of São Paulo and of the Hospital Israelita Albert Einstein, Certificate of Ethical Appreciation Presentation (PCEA) number 64888017.3.0000.0086. Trial registration is RBR-9zgxzd.

### Setting

Patients with depression will be recruited in the southern region of the São Paulo city at the Basic Health Unit (BHU; i.e., Arariba Park) in the state of São Paulo, Brazil. This BHU is part of the Brazilian Unified National Health System. First, patients will be referred by the physician team of the BHU if they fulfil the criteria of being 40 years and older, being treated for depression, and have no absolute contraindication to perform physical exercise. After the initial screening, patients will be fully informed of the procedures involved in the present trial and invited to sign an informed consent form. Participants will visit the laboratory on six occasions to perform the following assessments (Fig. 2):Visit 1: Consent form and anamnesis, Mini International Neuropsychiatric Interview (MINI) [52], and MADRS scale [28]. The number of depressive episodes in life and medicine dosage in the last 3 months (necessary clinical adjustments) [53] will be assessed by a trained psychiatrist researcher. Patients diagnosed with depression (single episode or recurrent episodes) will be referred to Visit 2. Patients will be informed that they may terminate their participation in this trial at any time, regardless of the reason.Visit 2: Questionnaire of cognitive function, suicidal ideation and behavior, hopelessness, and sleep quality.Visit 3: Blood samples after a 12 h fasting, functional tests, and instructions to use the accelerometer (GT9X ActiGraph accelerometer, Pensacola, USA) to assess sleep quality.Visit 4: these visits will be used to estimate the typical error of the functional tests (TUG test, TUG cognitive test, handgrip strength, 6-min walk test, body weight, hip and waist circumference); an interval of 48 h will be granted between Visits 3 and 4.Visit 5: Ergometric test and presence of absolute contraindications to exercise.Visit 6: MRI of the brain and instructions to use the accelerometer (GT9X ActiGraph accelerometer, Pensacola, USA) to assess physical activity level.

**Fig. 2 Fig2:**
[figure not shown]
Study design. First 4 weeks, the recruitment and initial test. For 24 weeks, the intervention period – training. Final 2 weeks, the Final tests. Visit 1 (V1): Consent form, Mini International Neuropsychiatric Interview (MINI), MADRS, number of depressive episodes in life, medicine dosage in the last 3 months (necessary clinical adjustments), and anamnesis. Visit 2 (V2): Questionnaire of cognition function, suicidal ideation behavior and sleep; Visit 3 (V3): Blood sample, functional tests, and accelerometer (sleep); Visit 4 (V4): functional tests. Visit 5 (V5): cardiorespiratory parameters; Visit 6 (V6): MRI of the brain and sleep quality (physical activity). After 24 weeks of intervention, all of the experimental groups will be reassessed at visit 7 to visit 11 (V7 to V11). V7: MRI of the brain and accelerometer (sleep); V8: blood sample; V9: MADRS, number of depressive episodes and medicine dosage; V10: Questionnaire of Cognition function, suicidal ideation behavior, sleep; V11: Functional tests and accelerometer (physical activity). At the end of the study, patient treatment costs will be estimated consulting the medical records of each patient. *HC* hip circumference, *WC* waist circumference

After 24 weeks of intervention, experimental groups will be reassessed in five visits (Visits 7–11; Fig. 2):Visit 7: MRI and accelerometer to assess sleep quality.Visit 8: Blood samples after 12 h of fasting.Visit 9: MADRS and necessary adjustments on medicine dosage [53] will be verified.Visit 10: Questionnaire of cognitive function, suicidal ideation and behavior, hopelessness, and sleep quality.Visit 11: Functional tests and accelerometer to assess the physical activity level.

At the end of the study, the patient treatment costs will be estimated [50, 54] by consulting the medical records of each patient.

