#### Clinical outcomes – scales of suicidal ideation, sleep, and BRIAN

The Columbia Suicide Severity rating scale distinguishes suicidal ideation from suicidal behavior. There are four subscales, namely severity of ideation (score of 0–5), intensity of suicidal ideation (score of 0–5), behavior (which is a nominal scale that evaluates actual, aborted, interrupted attempts, and self-injurious behavior, with no intent to commit suicide), and the fourth is the lethality of the actual attempts (scale score 0–6) [41].

The Scale of Hopelessness identifies the level of pessimism, which is directly related to the chance of developing several mental disorders and to suicide risk. The scale consists of 20 true–false questions. The total score is 20 points and each item is scored as 0 or 1 [42].

The Pittsburgh Sleep Quality Index score is a tool widely used for research and practice regarding psychiatric disorders [37]. This questionnaire interprets the perception of sleep quality in a feasible and reliable manner [37, 76]. The overall index is composed of seven components, namely subjective sleep quality (perception of sleep quality of subjects), sleep latency (time between lying on bed and sleeping), duration of sleep (sleeping period reported by the individual), sleep disturbance (sleeping problems), sleep medication (use of sleeping medications), and diurnal dysfunction (daytime sleepiness intensity). All the seven components are scored from 0 (no difficulty for the component of interest) to 3 (very bad). The scores on these components are combined to generate a global score that reflects the sleep quality and disturbances over a 1-month period. The overall score ranges from 0 to 21; if a patient reaches at least 5 points, they are diagnosed with an alteration of sleep. The higher the score the worse the quality of sleep.

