#### Treatment costs

Treatment cost for each patient will be determined using the methods described by Codogno [50, 54]. At the end of the trial, the demands for services and medicines recorded on medical records throughout the 6 months of the intervention period will be considered. The following information will be obtained: medicines supplied to the patient, laboratory tests performed, and the number of consultations throughout the intervention period. In addition, patient costs will encompass the cost of administrative and maintenance services related to the BHU where the procedures will be performed. The costs stipulated for these services and the number of patients attended will be added to the costs of each patient, according to the number of days that they visited the BHU over the 6-month period. In order to transform the procedures into actual currency, the values informed by the Municipal Health Department for the year 2018 will be used.

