Power calculations were performed using data published by Kerling et al. [88] (effect size 0.25), who showed that an aerobic exercise program can positively change depression scores as assessed by the MADRS scale. The obtained sample size was 21 patients per group (power 0.85, alfa error 0.05, correlation between repeated measures of 0.8). Assuming a drop-out ratio of approximately 30%, we will determine 25 patients per group as appropriate.

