### Ethics and dissemination

This trial is approved by the ethics committee of the Hospital Israelita Albert Einstein and the Department of Health of the city of São Paulo (CAAE) number 64888017.3.0000.0086. Trial registration is RBR-9zgxzd. According to Brazilian legislation, individual data will be stored for 5 years, and patient identification will not be made publicly available. As approved by the ethics committee, patients in need for ancillary care will be referred to the Brazilian public emergency service. As provided by the financing notice, at the end of the study the Principal Investigator should produce a research report with a focus on its use in the management of the Brazilian Unified National Health System.

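### Suicidal behaviour is counted after baseline only in patients who return for Visit 10; a few fields in the planned record review would cover all randomised patients at little cost

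*Protocol article*

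**What the plan says.** All references are to the Protocol article.

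- **Outcome.** Study design lists as secondary outcome 6 "suicidal ideation and behavior assessed by the Scale Columbia of Suicide score", together with a hopelessness scale. The section on the scales of suicidal ideation says that the behaviour subscale "evaluates actual, aborted, interrupted attempts, and self-injurious behavior". A further subscale grades the lethality of actual attempts.
- **Timing.** The baseline measurement is in Setting: "Visit 2: Questionnaire of cognitive function, suicidal ideation and behavior, hopelessness, and sleep quality". The second and last comes after the intervention: "After 24 weeks of intervention, experimental groups will be reassessed in five visits", with "Visit 10: Questionnaire of cognitive function, suicidal ideation and behavior, hopelessness, and sleep quality". Nothing is scheduled for this outcome between these two visits.
- **Drop-out.** Setting lets patients leave at any time. Data analysis and power calculations goes from 21 to 25 patients per group: "Assuming a drop-out ratio of approximately 30" per cent.
- **Missing values.** The same section removes missing values in a first analysis. It adds a second analysis that incorporates them if their incidence is high.
- **Records.** Setting has each patient's medical record consulted at the end of the study. Treatment costs fixes the window: "the demands for services and medicines recorded on medical records throughout the 6 months of the intervention period will be considered". The items listed are medicines, laboratory tests and consultations.
- **Emergency care.** Ethics and dissemination says that "patients in need for ancillary care will be referred to the Brazilian public emergency service". It does not link these referrals to the suicidal-behaviour outcome.

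**The concern.** A questionnaire score can be missing for reasons unrelated to its value. An attempt or an act of self-injury is different, because the event itself can be why the patient does not come back. With one ascertainment about 24 to 30 weeks after the first, the recorded events are those that attenders report. A death by suicide, the most serious form of the outcome, cannot be recorded at an interview.

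The article hypothesises a benefit of motor-complex exercise on suicidal behaviour, and the trial must report to the management of the public health system. A count taken from attenders could be read as a count for everyone randomised.

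**Working it through.** **Inputs from the article:** 75 patients in three groups of 25; drop-out of about 30%; one post-baseline measurement, at Visit 10.

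**Inputs assumed:** the event risk over 24 weeks and the ratio of risk in drop-outs to risk in completers (RR). The article gives neither. Drop-out is read as no reassessment, which the article does not say, so the counts below are upper bounds at 30%.

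**Step 1: the plan's own drop-out figure.** Allowing for 30% loss would turn 21 into 21/(1 − 0.30) = 30 per group. The planned 25 allows for 1 − 21/25 = 16%. The two figures disagree. That is a separate matter, but it gives a range:

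- at the stated 30%: 0.30 × 75 = 22.5 patients without a Visit 10 record (7.5 per group);
- at the implied 16%: 4 per group, 12 of 75.

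**Step 2: share of patients with an event who are missed.** With drop-out d, share = d·RR / [(1 − d) + d·RR].

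**Step 3: what that does to the count and the proportion.** Take d = 0.30 and an assumed 5% risk in completers. Counted: 52.5 × 0.05 = 2.6. Missed: 22.5 × 0.05 × RR.

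| RR (assumed) | Missed, d = 0.30 | Missed, d = 0.16 | True events in 75 | Counted | True proportion | Proportion in attenders |
|---|---|---|---|---|---|---|
| 1 | 30% | 16% | 3.75 | 2.6 | 5.0% | 5.0% |
| 2 | 0.6/1.3 = 46% | 0.32/1.16 = 28% | 4.9 | 2.6 | 6.5% | 5.0% |
| 3 | 0.9/1.6 = 56% | 0.48/1.32 = 36% | 6.0 | 2.6 | 8.0% | 5.0% |

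At RR 1 the count is too low but the proportion among attenders is unbiased. The proportion is too low only if drop-outs carry higher risk.

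**Step 4: more extreme assumptions.** At 10% in drop-outs and 3% in completers, 2.25 events are missed and 1.575 seen: 2.25/3.825 = 59%. At 15% and 3%: 3.375/4.95 = 68%. These shares describe only about 4 to 5 events in the whole trial.

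**Step 5: between arms.** Let completer risk be 5% and RR 3 in every arm, with drop-out of 40% in control and 20% in an exercise arm (assumed). True risks are 5% × (0.6 + 0.4 × 3) = 9% and 5% × (0.8 + 0.2 × 3) = 7%. Attenders show 5% in both, so a true difference of 2 percentage points disappears. Swapping the drop-out rates reverses the error. With equal drop-out and equal RR, the ratio between arms is preserved.

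**The case against.** **Events sent to emergency care.** A reader might infer that these are lost. The documents do not support that. A patient treated in week 10 who attends Visit 10 can report the attempt on the Columbia scale; the article gives no recall window that would exclude it. Loss is certain only for non-returners.

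**Bias toward safety.** A reader might also infer that the outcome is biased toward showing safety. That needs higher risk in drop-outs, which is an assumption. A distorted comparison between arms needs drop-out, or its relation to risk, to differ by arm, and either direction is possible. The article also treats this as a hypothesised benefit and draws no safety conclusion from it.

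**Unequal contact.** Exercise patients have two supervised sessions a week for 24 weeks (48), and controls only usual clinic visits. No informal observation feeds a planned outcome, and all groups get the same questionnaire from blinded assessors. This point falls away.

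**Condensed article.** Adverse-event recording may be in a full protocol that is not shown, so its absence here is no finding. The point rests instead on the stated instrument and visit schedule, which a separate adverse-event log would not change.

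**Meaning of drop-out.** The article does not define it, and some patients who stop training may still be reassessed. This stands, and it is why 22–23 is an upper figure under the 30% assumption.

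**Second analysis.** The analysis incorporating missing data is relevant, but a model cannot recover an event that nobody ascertained.

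**Few events.** Even full capture would give too few to compare arms. This stands and limits what the fix can claim.

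**Conclusion.** The point holds as a cheap improvement. On the stated schedule, a suicidal event in a patient who does not return is not counted and a fatal one cannot be, so the count is understated whenever such an event occurs. Up to 22–23 of 75 patients are affected if the 30% drop-out means no reassessment. The share of patients with an event who are missed is then 30% at equal risk and 46% to 56% at an assumed RR of 2 to 3. The 59% and 68% figures are arithmetically right, but rest on event rates with no source in the documents and should not be quoted as expected losses.

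The proportion among attenders and the comparison between arms may be biased, in a direction that cannot be determined. With about 17.5 attenders per arm, one patient is about 6 percentage points (1/17.5 = 5.7%), so a single unrecorded event could visibly change an arm's result.

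**What to change.** Keep the Columbia scale at Visits 2 and 10 as the stated outcome, and label its post-intervention result as one in attenders. As a supplement that does not redefine the outcome:

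1. Add to the end-of-study record review a few fields, extracted by someone blind to arm, covering randomisation to week 24: recorded suicide attempt, self-injury, psychiatric emergency or admission, and death.
2. Add the emergency referrals under Ethics and dissemination that are known to the trial.
3. Report these descriptively, as counts by arm with all randomised patients as the denominator.

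The cost is slight extra extraction in a review already planned for each patient over the same six months. Its limits should be stated. Health-unit records may miss events treated elsewhere or never brought to care, and the few events expected will not support a formal test between arms. No change to sample size, visits or treatment is needed.
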